## Abstract

**Background:**

Low back pain (LBP) is a common health problem and a substantial part of LBP is presumed to be attributable to degeneration of the intervertebral disc. For patients suffering from intractable discogenic LBP, there are few evidence-based effective interventional treatment options available. In 2010, the results of a randomized controlled trial (RCT) were published concerning “intradiscal methylene blue injection” (IMBI), in which this intervention appeared to be very successful in relieving discogenic pain. Therefore, we decided to repeat this study to investigate whether we could replicate the published results. The results of our preliminary feasibility study gave reason to set up an RCT. The aim of this RCT is to evaluate if IMBI is a more effective treatment of discogenic low back pain as an intradiscal placebo intervention, and furthermore, to assess the cost-effectiveness of this intervention.

**Methods/Design:**

Consecutive discogenic low back pain patients referred to four specialized pain treatment facilities are being screened for eligibility. After a positive standardized provocation discography and informed consent, patients are randomized into two groups. The treatment group receives an intradiscal injection with methylene blue, lidocaine, and contrast, and the control group receives intradiscal isotonic saline with lidocaine and contrast.

Main outcome measures are pain at the 6-month follow-up, patient’s global impression of change, cost-effectiveness, quality of life, disability, and analgesic intake.

**Discussion:**

The importance of this study is emphasized by the fact that for intractable discogenic low back pain patients, evidence-based effective pain treatments are rare. If this study establishes clinical success and cost-effectiveness, IMBI could become the “pain treatment of choice” for a selected group of patients with chronic discogenic low back pain for whom noninvasive treatment options have failed.

**Trial registration:**

National Trial register NTR2547

Registered at 29 September 2010 and 31 March 2014.

## Background

Low back pain (LBP) is a common health problem; more than 70 % of the population in industrialized countries will experience low back pain at least once in their life [1]. In most patients, LBP is assumed to resolve spontaneously, although in a recent systematic review it was shown that 60 % of patients who went to the general practitioner for their recent onset LBP, still suffer from back pain one year later [2]. LBP diminishes the quality of life of the individual patient substantially [3]. Furthermore, low back pain is also an economical problem for it imposes a substantial financial burden on society [4–7]. A substantial part of LBP is presumed to be attributable to degeneration of the intervertebral disc [8–10]. In a normal disc, nerve fibers are present only in the outer layers of the annulus fibrosis [11]. In contrast, in a degenerated disc, nociceptive nerves have been shown to grow into the inner layers of the annulus fibrosis along degenerative fissures [12–14]. Stimulation of these nerve endings with inflammatory mediators is assumed to produce pain [13, 15]. A positive provocative discography along with morphologic signs of disc degeneration, that is, annular tear grade II to IV according to the modified Dallas Classification, as seen during the discography procedure, is assumed to confirm the diagnosis of discogenic pain [16].

The treatment of discogenic chronic low back pain remains controversial. Patients who do not respond to conservative therapy may undergo various treatments, varying from interventional chronic pain treatment to fusion surgery, generally with variable and unpredictable results [17].

In 2010, results of a randomized placebo-controlled trial concerning intradiscal methylene blue injection (IMBI) were published [18]. It showed a clinically meaningful pain reduction in 89 % of IMBI-treated patients.

The rationale for this treatment is that methylene blue (MB) is neurolytic. Intradermal MB injection has shown by electron microscopy to be able to destroy dermal nerve endings [19]. By injecting methylene blue into the nucleus pulposus, it spreads into radial fissures where it can destroy the nerve endings or nociceptors that have grown into the painful disc. The authors and commentating author concluded that this treatment was promising but that it is imperative that more high-quality studies are performed to determine whether the results of this study can be reproduced.

In 2011, the Departments of Anesthesiology and Pain Medicine of Maastricht and Arnhem in the Netherlands started a pilot study to acquire information about effect size, recruitment strategies, acceptability of intervention, study burden, and safety of IMBI. The pilot indicates that IMBI could be effective (40 % responded to the treatment) in a well-selected group of patients suffering discogenic pain.

The proposed placebo controlled randomized clinical trial (RCT) was designed to investigate whether the results of the aforementioned RCT on IMBI can be replicated and additionally, to assess the cost effectiveness of this intervention.

## Methods/Design

A double-blind placebo controlled randomized clinical trial (RCT) will be conducted in four interventional pain centers in the Netherlands by certified pain specialists. The RCT is approved by European Union Drug Regulating Authorities Clinical Trials (EudraCT) and the medical ethics committee (METC) of the Maastricht University Medical Centre; registration number NL325 11.068.10 and 10-2-055, respectively. Informed consent will be obtained from all participants.

This study is sponsored by ‘The Netherlands Organisation for Health Research and Development’ (ZonMw), registration number 836011026.

Clinical trials registration number is NTR2547.

### Study population

Consecutive patients with chronic lumbar axial pain referred to the specialized pain centers are assessed for eligibility. Eligibility criteria are a history consistent with lumbar discogenic pain (for example, predominant axial pain produced on lumbar motion, significant functional limitation in sitting duration and tolerance); low back pain for at least 6 months, and in at least the last 6 weeks a poor response to treatment that is, analgesics, physiotherapy, facet blockade and radiofrequency therapy; age between 18 and 66 years; neurological exam without motor deficit; pain intensity of at least 5 measured with the Numeric Rating Scale (NRS) 1 to 10 [20].

Exclusion criteria are discogenic pain confirmed on more than two levels; extruded or sequestered herniated nucleus pulposus; previous lumbar surgery or invasive intradiscal procedures on suspected levels; symptomatic lumbar spinal stenosis; grade 1-2 spondylolisthesis. Further exclusions include BMI (Body Mass Index (kg/m^2^)) of ≥ 35, pregnancy, coagulopathy or oral anticoagulant therapy (except low-dose acetylsalicylic acid) in conditions that do not allow for a temporary discontinuation, and infection. Patients who are incapable of following verbal or written instructions or with psychiatric problems potentially interfering with cooperation in the study will be excluded as well.

Magnetic Resonance Imaging (MRI) must have been performed in the last 12 months before inclusion to rule out severe disc degeneration as evidenced by a > 50 % disc height loss at the affected level [21]. Patients undergo a provocative discography to confirm or rule out discogenic origin of the lumber pain [22–24]. The provocative discography will be conducted according to ISIS/IASP guidelines and with the use of a pressure- and velocity-controlled disc stimulation device (CDS) (Neurotherm™, Wilmington DE, US) [23]. In provocative discography, annular tears according to the Modified Dallas classification of annular tears scheme grade 1 to 4 (see Table 1) in either one, or at most two, discs must be present [13, 21]. Concordant pain provocation must be present in the disc(s) at pressures of less than 50 PSI above opening pressure, of at least NRS 7 (of 10) or ≥ 70 % reproduction of worst spontaneous pain [25]. At least one adjacent lumbar disc should perform as a negative control disc.

**Table 1 Tab1:** Modified Dallas Classification [16]

Grade	Grade Description
0	Contrast is within the nucleus
1	Extravasation in the inner 1/3 of the annulus
2	Extravasation in the middle 1/3 of the annulus
3	Extravasation in the outer 1/3 of the annulus
4	More than 30 degrees of annular circumference
5	Extra-annular contrast

Patients who fulfil the eligibility criteria for this study are asked to participate in the study.

### Intradiscal methylene blue injection (IMBI) versus placebo

After written informed consent, patients will be randomized 1:1 for the treatment or control group Fig. 1. The treatment will be performed in the daycare surgery facilities of the participating specialized pain centers. To standardize this procedure and to ensure equal quality of treatment application, all participating physicians are trained in performing the IMBI intervention according to protocol.

**Fig. 1 Fig1:**
[figure not shown]
Trial design and patient flow

Intradiscal methylene blue injection (IMBI) treatment consists of intradiscal injection with 1 ml of methylene blue, 0.5 ml of lidocaine hydrochloride 2 %, and 0.5 ml contrast dye (Iohexol-Omnipaque 300). The placebo treatment consists of 1 ml isotonic saline, 0.5 ml contrast dye, and 0.5 ml of lidocaine hydrochloride 2 %. This solution will be injected in the affected disc(s) under control of pressure (maximum of 100 PSI), velocity (0.02 ml/s), and volume using a CDS. During this procedure, the patient remains blind for the study-fluid. After the treatment, the patient has bed rest for at least 2 hours and during that time will be held in observation at the daycare surgery unit. Data will be collected at 6 weeks and at 3, 6, 12, and 24 months after the intervention, and patients will be seen by a physician or research nurse at each time-point to monitor patients’ adherence to the protocol.

### Allocation concealment

Both patients and post-intervention observers, such as pain managing nurses and physicians, are to remain blinded to the treatment or control intervention for at least 6 months. Therefore, during the intervention the interventional pain specialist takes care that the patient does not see the injected fluid. By asking the patient half an hour after the procedure what medication they think they received - either 1) methylene blue, 2) placebo or, 3) “I really don’t know” - the efficacy of the blinding procedure shall be checked. Furthermore, the same question will be repeated in the online patient questionnaire at 6, 12, and 24 weeks. Six-months post-intervention, at the patient’s request, patients from the control group who still suffer pain can receive the IMBI treatment.

### Objectives

Patients are assessed at baseline, at 6 weeks, 3 months, and at the primary end-point of 6 months, and furthermore, at the follow-up of 12, and 24 months.

Primary outcome measures is average pain at 6 months, measured by a pain diary with numeric rating scales (NRS) three times a day for 4 consecutive days. Success of the intervention is defined as pain reduction of at least 30 % at 6 months.

Other study variables include the Patients Global Impression of Change (PGIC) measured by a 7-point Likert Scale and number of adverse and serious adverse events [26]. Societal cost consisting of hospital cost and costs outside the hospital are measured by means of cost questionnaires. Disability is measured by the Oswestry Disability Index [26], Quality of life (QOL) by the Rand-36 and EQ-5D [26]. Information about pain characteristics is collected using the McGill Pain Questionnaire [26], and information about analgesics use with a diary at each time-point for 4 days. The potential predictive value, for success or failure of the intervention, will be explored with use of baseline variables, MRI classification, and registered variables of the provocative discography [26, 27].

With the exception of the pain and medication diary, and the health-related quality of life EuroQol (EQ-5D) questionnaire, which are presented to the patient in a booklet, all data will be collected by web-based questionnaires software, SelectSurvey. (NETv4.075.011© Copyright 2008 ClassApps.com) and MACRO (version 4.1.2.3750© 1999-2012 InferMed Limited, London, UK).

### Randomization and stratification

The randomization of study patients in either the treatment or the control group will be done with software for randomization of clinical trials ALEA (version 2.2 CTCM/ALEA). The stratification factors, that are used in the randomization procedure to assure that potential confounders are equally distributed between the two randomized groups, are study center; gender; dichotomized disc levels (1) L3/L4 to L4/L5 and (2) L5/S1; and dichotomized Modified Dallas criteria (1) 1 to 2 and (2) 3 to 4. The software automatically sends an e-mail with the randomization results to the un-blinded physician who will perform the IMBI treatment.

### Sample size

The sample size of the RCT is determined on the basis of success rates in the previous RCT [18] and our pilot [28]. We assume that 50 % of patients in the treatment group will be successfully treated. Success is defined as 30 % pain reduction at the 6-month follow-up. In the control group, we assume a 20 % success rate.

Given the invasive character of the IMBI procedure, we consider that the treatment group should be at least 30 % more successful than the control group to reach minimally clinical relevance. Furthermore, we assume 10 % drop out per group.

For a power of 80 % and a level of statistical significance of 5 %, the minimum sample size is under these assumptions estimated to be 80 patients, that is, 40 per randomized group [29].

### Sample size interim analysis

Given the invasive character of IMBI and the burden for the patients, an interim analysis is pre-planned to test whether we can stop the study preliminarily assuming that the experimental group has a higher success rate than the control group and to monitor planned sample size assumptions. The sample size calculation for the interim analysis is based on the assumption that a success rate of 20 % in the placebo group is probably too high. Therefore, we assume a success rate of 10 % at 6 months in the placebo group, instead of 20 % success. If we detect a difference in success rate of 40 % between the two groups, the sample size is estimated to be 50 patients, that is, 25 per randomized group with a power of 90 % and a level of statistical significance of 2.5 % (one-sided).

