
### Monitoring

#### Data Monitoring Committee (DMC)

The major task of the DMC is safety monitoring. Any serious adverse event or suspected unexpected serious adverse reaction, which might be life threatening or liable to produce disability or deformity, is an indication to set up a DMC meeting. Another important task for the DMC is monitoring the efficacy for futility and monitoring the planned sample size assumptions, whether criteria for early stopping are met. The statistician of the DMC will be the only one during the trial who has access to the un-blinded data. He performs the (interim) analyses. Members of the DMC are (1) head of the department of orthopedic surgery and (2) statistician and internal medical specialist of Maastricht University Medical Centre (MUMC) the Netherlands. Each member has no conflicts of interest with the study or the study members. The advice(s) of the DMC will be notified upon receipt by the research committee to the METC that approved the protocol. With this notification a statement will be included indicating whether the advice will be followed.

This RCT will be audited and monitored by the Clinical Trial Centre Maastricht (CTCM); this organization is independent from the investigators and sponsor.

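### The interim efficacy look and the final test carry uncoordinated significance levels: used as stated, both test at z = 1.96, and false claims of benefit run at about 3.9% rather than 2.5%

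*Protocol article*

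**What the plan says.** Four places in the protocol article bear on this point.

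- **Sample size interim analysis** gives the purpose: "an interim analysis is pre-planned to test whether we can stop the study preliminarily assuming that the experimental group has a higher success rate" than control, together with a check on the sample size assumptions. It assumes 10% success on placebo and a 40-point difference, hence 50% v 10%. The size and level are "25 per randomized group with a power of 90 % and a level of statistical significance of 2.5 % (one-sided".
- **Sample size** sets the final analysis: "For a power of 80 % and a level of statistical significance of 5" %, the size is "estimated to be 80 patients, that is, 40 per randomized group". The assumed rates are 50% on treatment ("We assume that 50 % of patients in the treatment group will be successfully treated") and 20% on control ("In the control group, we assume a 20 % success rate"), with 10% dropout per group. The sidedness of the 5% is not stated, and nothing is deducted for the interim.
- **Statistical analysis** names a chi-square test on success, defined as at least 30% pain reduction at 6 months. It gives no significance level, adjusted or otherwise.
- **Data Monitoring Committee (DMC)** gives the committee the task of "monitoring the efficacy for futility and monitoring the planned sample size assumptions, whether criteria for early stopping are met". The criteria themselves are not printed.

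**The concern.** A look that can end the trial with a claim of benefit uses up part of the permitted false-positive rate. The final test must then be run at a reduced level, or the interim at a much stricter one. Here the interim level equals the benefit-side half of a two-sided 5% test, so the full allowance for a false claim of benefit is available at 50 patients and again at 80, on the same endpoint.

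The 5% would then not be the error rate of the design. This matters because the trial is meant to find out whether a strikingly positive earlier result (89% success) can be replicated. A marginal early stop would be open to the objection that it came from an unadjusted extra look.

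**Working it through.** **1. Reproduce the stated sizes.** Take two proportions, unpooled variance and normal approximation, then divide by 0.9 for the 10% dropout:

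n = [p1(1-p1) + p2(1-p2)] × (z_alpha + z_power)² / (p1-p2)²

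- Interim, 50% v 10%, one-sided 2.5%, 90% power: 0.34 × (1.960 + 1.282)² / 0.16 = 22.33; 22.33/0.9 = 24.81, so **25**, as stated.
- Final, 50% v 20%, two-sided 5%, 80% power: 0.41 × (1.960 + 0.842)² / 0.09 = 35.76; 35.76/0.9 = 39.73, so **40**, as stated.
- Final with one-sided 5%: 0.41 × (1.645 + 0.842)² / 0.09 = 28.16; 28.16/0.9 = 31.29, so 32, not 40.

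The formula is inferred, but one method returns both stated sizes when the final 5% is two-sided. The pooled-variance version without dropout gives 26 and 39, which points the same way.

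**2. Compare critical values.** One-sided 2.5% is z = 1.960, and two-sided 5% is also z = 1.960.

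**3. Error rate over two looks.** The information fraction is t = 50/80 = 0.625 (also 45/72 if dropout applies at both looks). Under no effect, the two statistics are approximately bivariate normal with correlation sqrt(0.625) = 0.791.

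| Reading | Expression | t = 0.625 | t = 50/72 = 0.694 |
|---|---|---|---|
| False claim of benefit (nominal 2.5%) | 1 - P(Z1 < 1.96, Z2 < 1.96) | 3.9% | 3.8% |
| Benefit-only interim, two-sided final (nominal 5%) | 1 - P(Z1 < 1.96, -1.96 < Z2 < 1.96) | 6.4% | 6.3% |
| Benefit-only interim, final one-sided 5% | 1 - P(Z1 < 1.96, Z2 < 1.645) | 6.0% | 5.8% |

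**4. Check with the chi-square test itself.** Exact enumeration, without continuity correction, 25 then 40 per group:

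| Success rate in both arms | Single look at 40, two-sided | Two looks, benefit | Two looks, overall |
|---|---|---|---|
| 10% | 5.9% | 4.3% | 7.2% |
| 20% | 5.1% | 4.2% | 6.7% |
| 30% | 4.8% | 4.0% | 6.4% |

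At 10%, about 0.9 of the 2.2-point excess over 5% is already present with a single look. It comes from the discreteness of the test, not from the interim.

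**5. A spending rule that holds the level.** The Lan-DeMets O'Brien-Fleming-type function at one-sided 2.5% spends 2 × [1 - Phi(2.2414/0.7906)] = 0.0046 at t = 0.625, so z = 2.61 at the interim. Solving 1 - P(Z1 < 2.61, Z2 < c) = 0.025 gives c = 1.985, which is two-sided p = 0.047 at the final.

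**6. What the rule does to power (exact).**

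| | z = 1.96 | With the rule |
|---|---|---|
| Interim, 50% v 10%, 25 per group | 91% | 74% |
| Interim, 50% v 10%, 22 per group | 86% | 65% |
| Trial, 50% v 20%, 40 per group | 81.7% (single look) | 82.0% (both looks) |
| Trial, 50% v 20%, 36 per group | 78.6% (single look) | 77.5% (both looks) |

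The small gain at 40 per group should not be read as a benefit. The discrete test has the same single-look power, 81.7%, at z = 1.96 and z = 1.985, so the interim look only adds to it.

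**The case against.** The strongest reply is that the protocol never prints a stopping boundary or a level for the final test. The 2.5% and the 5% are both inputs to sample size calculations, and the Statistical analysis section gives no level. The DMC section refers to early-stopping criteria, and a journal article may leave these to an analysis plan or a committee charter. This stands to the extent that a reader who infers that the trial's false-positive rate is certainly above its nominal level goes further than the text. It does not remove the point. These are the only levels given, and an adjusted boundary held elsewhere would not match the inputs used here: at the rule in step 5, 25 per group no longer has 90% power.

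Other stronger readings are tempting and are not supported:

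- **That 7.2% is the inflation caused by the interim.** Part of it is discreteness (step 4).
- **That overall error is 7.9%.** That figure needs a two-sided interim, and the protocol calls its interim one-sided.
- **That the whole alpha is spent at the interim on any reading.** This holds for the benefit direction if the final test is two-sided. If it is one-sided 5%, half is spent, and the overall rate is still about 6.0%.
- **That no result at 50 patients could be claimed at 5%.** The result the interim was sized for, 50% v 10% with 25 per group, gives z of about 3.09, above the adjusted 2.61.
- **That the two statements of purpose are incompatible.** A futility remit can sit beside an efficacy look, and futility stopping does not inflate type I error. The passages simply do not describe the same task.

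Finally, the 40-point difference could be taken as the stopping condition itself. An observed difference that large has a null probability of at most about 0.33% at success rates of 10% to 50%, so the inflation would be negligible. The sentence reads more naturally as the difference assumed for sizing, but the fact that both readings are possible is a further reason to state the rule.

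**Conclusion.** The point holds as a conflict between levels the protocol itself states, not as a complaint about missing detail. If those levels are the test levels, false claims of benefit are about 3.9% against 2.5%, and overall error is about 6.4% against 5%. If the final 5% is one-sided, the overall figure is about 6.0%. The inflation is moderate.

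It rests on three assumptions: the 2.5% serves as the efficacy boundary; the final test is run at the 5% used for sizing (two-sided by the protocol's own numbers); and information at the interim is about 50/80. Moving to 50/72 changes little. The stated sizes of 25 and 40 per group are not wrong in themselves. The fault is the pairing of the two levels. The difference between the interim's efficacy purpose and the committee's futility remit is secondary.

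**What to change.** State one alpha-spending rule covering both looks, before any unblinded interim result is seen. One example is the O'Brien-Fleming-type Lan-DeMets function at 50/80: stop for efficacy only if one-sided p <= 0.0046, and test the final at two-sided p <= 0.047. Both limits are to be recalculated if the actual information fraction differs; at 50/72 they would be about 0.0072 and 0.0456. Other valid rules would serve. A Pocock-type constant bound, for instance, is two-sided 0.0311 at both looks, but it raises the final size by the protocol's formula to 46 per group.

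State the sidedness of the final 5%, and say whether the 40-point difference is a sizing assumption or a stopping condition. Restate the interim power: under the O'Brien-Fleming-type rule, 25 per group gives about 74% at 50% v 10% (about 65% with 22 evaluable), so the stated 90% cannot remain.

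Bring the interim section and the DMC section into line on whether the look serves efficacy, futility or both. No particular futility threshold is required.

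The cost is small. The final size by the protocol's formula moves from 40 to 41 per group (36.40/0.9 = 40.44), and the power of the trial is essentially unchanged. The real price is a stricter bar for stopping at 50 patients, and so a lower chance of stopping early.
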